#### Quality of life

Quality of life will be evaluated with the The *EuroQol 5-Dimensional questionnaire* (EQ-5D-5L), which consists of questions related to five health domains (pain, mood, mobility, self-care and daily activities), yielding an overall quality of life score. Participants’ opinion on their own current health status will also be evaluated using a visual analogue scale ranging from 0 (worst imaginable health status) to 100 (best imaginable health status). The EQ-5D-5L is a widely accepted and standardized tool to measure health-related quality of life in diabetic subjects [46].

#### Healthcare resources

Healthcare resources consumption will be evaluated using a tailored questionnaire, specifically designed for the study to assess direct medical costs of: outpatients visits to specialist physicians, hospital admissions, emergency room visits, use of homecare services, visits to GPs, and use of medications and laboratory examinations.

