## Methods

### Objectives

The ‘TRIPL-A’ study (i.e., a TRIal to promote PhysicaL Activity among patients in the young-old age affected by type 2 diabetes) aims to assess if realizing an innovative ERS based on a strong partnership among GPs, specialist physicians, exercise specialists, and patients, and supported and facilitated by a multi-platform WBA, can effectively lead older sedentary T2D patients to adopt an active lifestyle.

We hypothesize that this ERS will be able to reduce inactivity time and the use of healthcare resources.

Accordingly, the primary objective of the trial is to determine if the ERS reduces sedentary behaviors, while the secondary objectives are to determine if it increases the patient’s physical activity level, fitness status, metabolic profile, psychological well-being, and quality of life, while reducing the use of health care services.

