### Assessments/outcomes

Patients’ anthropometrics, sedentary habits, PA level, fitness status, metabolic profile, psychological well-being, quality of life, and use of health-care resources will be assessed, along with other routine assessments, on four separate occasions: at baseline and at 6, 12, and 18 months from baseline (see Table 3). The difference between the intervention and control arms at the 12-month time-point will be considered the main outcome for each measure.

**Table 3 Tab3:** Timing of study assessments

	Screening	Visit 1 baseline	Visit 2 follow-up 1	Visit 3 follow-up 2	Visit 4 follow-up 3
Weeks from randomization	-2	0	24	48	76
Visit window in weeks	–	+ 2	+/− 2	+/− 2	+/− 2
Informed consent	X				
Demographics	X				
Inclusion/exclusion criteria	X	X			
Anthropometric measures		X	X	X	X
Clinical variables		X	X	X	X
Randomization		X			
Lifestyle counseling		X			
Lifestyle informative material		X			
WBA training (only for intervention group)		X			
Blood pressure		X	X	X	X
Registration of laboratory assays		X	X	X	X
LDCW		X	X	X	X
IPAQ (short form)		X	X	X	X
EQ-5D-5L		X			X
PSQI		X			X
Healthcare resource consumption		X	X	X	X
Events					
Adverse events including hypoglycemia		X	X	X	X
New diagnoses		X	X	X	X
Intervention compliance check			X	X	X
Trial completion					X

Notes: *LDCW* long distance corridor walk, *IPAQ* International Physical Activity Questionnaire, *EQ-5D-5L* Euro Quality of Life 5 Dimensional questionnaire, *PSQI* Pittsburgh Sleep Quality Index

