### Statistical methods

#### Sample size calculations

The sample size has been calculated to test the hypothesis of no difference in sitting time per day between intervention and control arms at the 12-month time-point (2-sided independent sample t-test; statistical power 0.8; α level of significance 0.05; 1:1 ratio between intervention and control arm). Given an expected mean value of sitting time of 500 ± 200 min per day [39, 41–43], a sample size of 112 participants in each arm will be necessary to detect a difference of 75 min per day of mean sitting times between intervention and control arm. Therefore, it was assumed that a sample size of 300 participants, i.e. 120 in each arm accounting for an expected drop-out rate of 20%, is appropriate to obtain the desired statistical power.

Sample size was computed using STATA statistical software (StataCorp).

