#### Data analyses

*Intention to treat* analysis will be adopted to account for possible issues related to noncompliance and missing outcomes. Data quality and internal consistency will be assessed *ex-post* using Cronbach’s alpha. In addition, automatic routines will be performed on the data to detect possible outliers, which will be excluded from further analyses. Explorative univariate and bivariate data analyses will then be performed.

For each study outcome, the intervention and control arm will be compared, as the difference between baseline and 12-month time-point, using independent sample t-tests. A mixed-design ANOVA will be used to compare each study outcome between intervention and control arm at the four different time-points, followed by *post-hoc* pairwise comparisons when a significant interaction is found. Participants’ characteristics (e.g., age, sex, fitness status, physical activity level, and metabolic profile) will be used as covariates, and appropriate interaction terms will be assessed and may be included in the model. For all tests, 2-sided *p* values with an α level of significance of 0.05 will be used. Bonferroni’s criterion will be used to adjust the overall α level to correct for multiple tests.

The assumptions of each statistical test will be assessed before analyses and, if not met, either data transformation will be performed or alternative statistical methods will be adopted (e.g., GEE, mixed-models, non-parametric analyses, etc.) will be performed. The residuals and goodness of fit of the models will also be examined.

SPSS Statistics (IBM) and R (R Core Team) software will be used to perform data analyses.

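### Health-care use accumulates over time, but its main test is a 12-month change score; baseline-adjusted total use since randomisation would suit it better

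*Protocol article*

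**What the plan says.** The Objectives section puts health-care use into the trial's single hypothesis: "We hypothesize that this ERS will be able to reduce inactivity time and the use of healthcare resources". It then ranks that outcome among the secondary objectives.

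The Healthcare resources section defines the measure: "Healthcare resources consumption will be evaluated using a tailored questionnaire, specifically designed for the study to assess direct medical costs". The components are specialist and GP visits, admissions, emergency visits, home care, medication and laboratory tests. No recall period is given.

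Table 3 (Assessments/outcomes) schedules the row "Healthcare resource consumption" at baseline and at weeks 24, 48 and 76. The text above the table names the arm difference at 12 months as the main outcome of every measure.

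The Data analyses section gives the test: "For each study outcome, the intervention and control arm will be compared, as the difference between baseline and 12-month time-point, using independent sample t-tests". It makes no exception for quantities that accumulate. The same section also plans:

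- a mixed-design ANOVA of every outcome over the four time-points, with participant characteristics as covariates and pairwise comparisons after a significant interaction;
- transformation, GEE, mixed models or non-parametric methods if assumptions fail.

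The Abstract mentions only repeated-measures ANCOVAs.

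**The concern.** A change from baseline to month 12 is a natural summary of a state, such as sitting time or HbA1c. Visits, admissions and costs are different: each report is a count or sum over some window. One report minus another is the change in use between two windows, not use since randomisation. If the windows run from visit to visit, the main contrast leaves out the first six months after randomisation and adds the sampling noise of a skewed pre-trial count.

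At stake is the sensitivity and meaning of the test of one of the two limbs of the hypothesis. The Discussion also rests part of its case on limited health-care budgets, for which use or cost per patient over a period is the relevant quantity.

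**Working it through.** **The plan's own figure.** The Sample size section assumes a "2-sided independent sample t-test; statistical power 0.8; α level of significance 0.05; 1:1 ratio between intervention and control arm", with an SD of 200 and a difference of 75 min per day. By the normal approximation, n per arm = 2 × 200² × (1.960 + 0.842)² / 75² = 111.6, which rounds up to the stated 112. With 20% drop-out, 300 × 0.8 / 2 = 120 per arm. These figures concern sitting time only. No variance, correlation, event rate or effect is stated for health-care use, so everything below rests on assumptions.

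**Share of reports used.** Assume recall since the previous visit. The post-randomisation intervals are then 24, 24 and 28 weeks. The 12-month change score uses only the second: one of two reports to month 12, one of three to month 18.

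**Information.** Assume equal variance (set to 1) at each report, equal correlation r between reports, and the same effect in each interval. The variances are:

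- A, change score at month 12: 2(1 − r)
- B, month-12 report adjusted for baseline: 1 − r²
- C, mean of the two reports to month 12, adjusted for baseline: (1 + r)/2 − r²

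| r | A | B | C | A/C, total gain | B/C, from adding interval 1 | A/B, from adjusting |
|---|---|---|---|---|---|---|
| 0.3 | 1.40 | 0.91 | 0.56 | 2.5 | 1.6 | 1.5 |
| 0.5 | 1.00 | 0.75 | 0.50 | 2.0 | 1.5 | 1.3 |
| 0.7 | 0.60 | 0.51 | 0.36 | 1.7 | 1.4 | 1.2 |

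A/C is the product of the last two columns, up to rounding.

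**Does the ANOVA repair it?** For illustration, take 120 per arm and a constant effect of 0.375 SD, borrowed from sitting time (75/200). The group-by-time interaction has 3 degrees of freedom and noncentrality (120/2) × 0.75 × 0.375² / (1 − r), which is 12.66 at r = 0.5.

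| r | Power: change-score t-test | Interaction | C |
|---|---|---|---|
| 0.3 | 69% | 71% | 97% |
| 0.5 | 82% | 86% | 98% |
| 0.7 | 96% | 98% | over 99% |

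The interaction does slightly better than the t-test and less well than the adjusted total.

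**Counts.** A simulation with gamma-Poisson counts (shape 0.7 to 1.5), a rate ratio of 0.75 and 120 per arm points the same way. At means of 1, 2 and 4 contacts per interval, the change-score t-test has roughly 28%, 50% and 78% power. A robust Poisson model of the two-interval total, adjusted for baseline, has roughly 57%, 81% and 96%. These inputs too are assumed.

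**Delayed effect.** Let the first-interval effect be a fraction k of the second. C loses its advantage over A when (1 + k)/2 falls below √(C/A), that is, when k is below 0.26, 0.41 or 0.55 at r = 0.3, 0.5 or 0.7.

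**Recall of 12 months.** The month-12 report then covers all of months 0 to 12. Only the adjustment gain A/B = 2/(1 + r) remains: 1.5, 1.3 or 1.2, with r now the correlation between two 12-month reports.

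**The case against.** The strongest reply is that the plan has a second analysis. The mixed-design ANOVA takes in the 6- and 18-month reports. A reader who stops at the t-test might infer that the plan ignores most of the use recorded after randomisation, and that is not so for the plan as a whole. What remains is that the interaction addresses a pattern over time rather than total use, and that 12 months is the declared main contrast.

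Second, the recall period is unknown. If the questionnaire asks about 12 months, nothing between randomisation and month 12 is lost. Even on visit-to-visit recall, the share left out by month 12 is half, not most. This stands, and it makes the point conditional.

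Third, part of the gain is the general advantage of adjusting for baseline over subtracting it. This also stands, and the table separates the two. Totals without adjustment would not always win: setting 2(1 − r) equal to (1 + r)/2 shows that the unadjusted 12-month total loses its advantage above r = 0.6.

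Fourth, the fallback methods may deal with skewness. They apply only if assumptions fail, and they change the model, not the period compared.

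Finally, exercise may act slowly, and the period to compare is partly a choice of estimand. That is fair, and the break-even values above show how much delay it would take.

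**Conclusion.** The point holds in a conditional form. The stated main contrast fits an accumulating outcome poorly, and no contrast of total use is named. Given visit-to-visit recall, equal variances, a constant effect and correlations of 0.3 to 0.7, baseline-adjusted use over months 0 to 12 has 1.7 to 2.5 times the information of the change score.

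Two stronger conclusions might be inferred and are not supported. One is that the information is halved: that is the value at an assumed r of 0.5, and the documents give no correlation or variance for this outcome. The other is that half of the trial is at risk. The outcome is one limb of the hypothesis but a secondary, unpowered objective, and the sitting-time calculation is untouched. Nor is a cost per patient out of reach: the change contrast does not give one, but the scheduled reports can be summed if their windows allow.

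This is a worthwhile change to a secondary analysis, not a threat to the trial.

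**What to change.** - Exempt health-care use and cost from the change-score rule in Data analyses and from the 12-month rule in Assessments/outcomes.
- Make total use and total cost from randomisation to month 12 the comparison, with totals to month 18 as a further contrast. Include baseline use and centre as covariates.
- For contacts, use a count model with robust errors and log follow-up time as offset. For costs, use a gamma-type model or a bootstrap, also allowing for follow-up time.
- State the questionnaire's recall period and confirm that successive windows join without gap or overlap. If they overlap, summing them would count some use twice.

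The cost is a few lines of wording and some extra analysis. No visit is added. If the questionnaire does not already cover the time since the last visit, its recall question needs a change. The one statistical drawback is dilution of the 12-month total if the effect is delayed.

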#### Metabolic profile

Blood fasting glucose and glycated hemoglobin (HbA1c) analyses will be used as indices of glycemic control. Since these tests are routinely performed on diabetic patients, they will be retrieved from the patients’ medical records, selecting the test that was performed closest to each assessment time-point.

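### The closest-test rule for HbA1c and fasting glucose sets no direction or limit, so read literally a baseline value may be drawn after randomisation; it should be reconciled with the allocation rule

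*Protocol article*

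**What the plan says.** Under Metabolic profile, the Protocol article gives HbA1c and fasting glucose as the indices of glycaemic control. The trial does not schedule the blood tests. "Since these tests are routinely performed on diabetic patients", "they will be retrieved from the patients’ medical records", and the value for each visit is found by "selecting the test that was performed closest to each assessment time-point". The section names no direction in time and no maximum distance, and does not bar using one result twice.

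Four other places bear on the rule:

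- **Assessments/outcomes, Table 3.** Visits fall at weeks 0, 24, 48 and 76. The row "Visit window in weeks" allows +2 weeks at baseline and ±2 weeks later, and it refers to visits. The laboratory row reads "Registration of laboratory assays" and is marked at Visits 1 to 4. Randomisation is also at Visit 1.
- **Enrollment and arm assignment.** The arm is assigned once baseline testing is complete. The section does not say whether a result retrieved from routine records counts as a baseline test.
- **Intervention arm.** Supervised training begins in month 1.
- **Data analyses.** Each outcome is "compared, as the difference between baseline and 12-month time-point", by independent-sample t-test. A mixed-design ANOVA over the four time-points follows, and metabolic profile is named among the covariates.

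**The concern.** A nearest-in-time rule with no direction treats a result from a few weeks after randomisation as equal to one from a few weeks before. In the intervention arm the later result may already contain some effect of training; in the control arm it does not. Subtracting it as baseline removes part of the effect being estimated. Using it as a covariate adjusts for something that allocation may have changed. Both errors push the arm difference toward zero. The trial is open, so the timing of routine tests after allocation could also differ between arms.

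Two smaller problems come from the missing limit. A follow-up value may lie far from its visit, and in rarely tested patients one result may be entered for two adjacent visits, which sets the change between them to zero.

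The primary outcome, sitting time from the IPAQ, is not involved. At stake is the trial's evidence on glycaemic control.

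**Working it through.** The article gives no figure on this point to reproduce. Its one calculation, the sample size for sitting time, does not bear on it.

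**Inputs.** Visit weeks 0, 24, 48 and 76 are from Table 3. Test spacing T is not in the article and is assumed: regular tests every T, with timing unrelated to visits. The time B over which the effect builds up is also assumed, with linear growth from randomisation and the full effect present at 12 months.

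**Literal rule at baseline.** The offset of the closest test is uniform on (−T/2, +T/2).

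- Probability that it falls after randomisation: 0.5 for any T.
- Probability that it falls more than 2 weeks after: (T/2 − 2)/T. For T = 12 weeks this is 4/12 = 33%; for T = 26 weeks, 11/26 = 42%.
- Mean post-randomisation offset, counting earlier tests as zero: (1/T) × (T/2)²/2 = T/8. For T = 3 months this is 0.375 month; for T = 6 months, 0.75 month.
- Share of the effect subtracted at baseline: (T/8)/B.

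| Build-up time B | T = 3 months | T = 6 months |
|---|---|---|
| 3 months | 0.375/3 = 12.5% | 0.75/3 = 25% |
| 6 months | 0.375/6 = 6.3% | 0.75/6 = 12.5% |
| 12 months | 0.375/12 = 3.1% | 0.75/12 = 6.3% |

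**Distance at 12 months.** The closest test lies within ±2 weeks of week 48 with probability 4/T: 4/12 = 33% at 12-weekly testing and 4/26 = 15% at 26-weekly testing.

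**Re-use.** One test is closest to two visits a gap g apart with probability max(0, 1 − g/T).

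- Weeks 0 and 24: 0% for T of 24 weeks or less; 1 − 24/26 = 7.7% at T = 26; 1 − 24/52 = 54% at T = 52.
- Weeks 0 and 48, the main comparison: 0% until T exceeds 48 weeks; 1 − 48/52 = 7.7% at T = 52.

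A simulation of 200,000 patients per test interval agreed with these formulas.

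**What a window would cost, at T = 26 weeks.**

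- ±6 weeks at follow-up keeps 12/26 = 46% of values. Adding a 12-week look-back at baseline leaves 10/26 = 38% of patients with a change from week 0 to week 48, because the last baseline test must then lie 0 to 10 weeks before randomisation.
- ±12 weeks at follow-up keeps 24/26 = 92% of values. On nominal weeks the windows are 12–36, 36–60 and 64–88, which do not overlap beyond a shared endpoint at week 36.

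**The case against.** The best defence is that the article, read as a whole, already excludes a late baseline. Allocation comes after baseline testing, and the assays are registered at Visit 1. A result not yet drawn cannot be registered then. On that reading the closest test means the closest one available at Visit 1, and the bias at baseline disappears.

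Much of this stands. A reader might infer that the protocol calls for baseline values from after randomisation, or that half the patients will have one. The documents do not support either. The 50% needs the literal reading and test times unrelated to visits. What survives is that the allocation section does not say retrieved routine results are baseline tests, and the Metabolic profile section carries no such limit. Two people extracting data could apply the text differently.

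Three further objections also have force:

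- The 12–25% loss assumes that the whole 12-month effect is reached in 3 months. Table 1 raises intensity and duration through period 5, so slower build-up is at least as plausible, and the loss is then 3–6%.
- A reader might infer that re-use of one result is general. It does not occur with regular tests 24 weeks apart or closer, and it is about 8% at 26 weeks.
- Windows and look-backs are often left to an analysis plan. That would excuse silence, but here the article states a selection rule, and its literal wording admits a biased value.

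**Conclusion.** The point holds as an ambiguity in a stated rule, with a known direction of bias if the rule is followed literally. It does not show that post-randomisation baselines will be used.

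Under the literal reading, with tests every 3 to 6 months at times unrelated to visits, the estimated effect on HbA1c and fasting glucose would shrink by about 3–6% if it builds over 12 months and by up to about 12–25% if it builds over 3 months. These figures rest on assumed test frequency and assumed linear build-up; the article supplies neither. If baseline results are in fact fixed before allocation, this loss is zero. The lack of a distance limit at follow-up remains in either case, and re-use remains a minor matter confined to test intervals above about 24 weeks. Only secondary outcomes are affected. The change is worth making because the part that removes the bias costs very little.

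**What to change.** Bring the Metabolic profile section into line with Enrollment and arm assignment:

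1. The baseline value is the last routine result dated on or before randomisation.
2. Each follow-up value is dated after randomisation and is the result closest to the visit within a wide window, for example ±12 weeks, about half the visit interval.
3. Each result is used for one visit only. The window nearly ensures this on nominal weeks. Actual visits may be as little as 24 − 2 − 2 = 20 weeks apart, so the rule should still be stated.
4. The draw date is recorded with each result.
5. These outcomes are analysed with a likelihood-based mixed model, which Data analyses already lists as an alternative.

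**Cost.** A few sentences and a recorded date, with no extra blood draw. Baseline values may be older, up to T before randomisation, which adds noise to both arms alike. Some follow-up values become missing, about 8% per visit at 26-weekly testing (1 − 24/26) and more if tests are rarer. The planned change-score t-test and a classical mixed-design ANOVA drop patients with a missing value, which is why item 5 is needed. Much narrower windows should be avoided: at 26-weekly testing, ±6 weeks would lose more than half of the follow-up values.

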#### Sleep disorders

Sleep disorders will be evaluated using the Pittsburgh Sleep Quality Index (PSQI) global score [47] (in which a score > 5 indicates poor sleep). The PSQI is a widely accepted tool to measure sleep-wake disturbances in diabetic patients. It assesses sleep quality, sleep latency, sleep duration, sleep efficiency, sleep disturbances, use of sleep medications, and daytime dysfunction [48].

#### Anthropometry

Height (head in the Frankfurt plane) and weight (light clothes, without shoes) will be measured with the patient standing and body mass index (BMI) will be calculated (kg/m^2^). Waist and hip circumference will be assessed using standard methods (as the average of triplicate measures) and waist-to-hip ratio (WHR) will be calculated.

